### Control group

Participants in the waitlist control group will be informed that they must wait 8 weeks before beginning the shared book reading sessions. Dyads in the control group will not be introduced during this 8-week period; participants with DS and students in this arm will only meet after the 8-week follow-up, when the intervention begins. To maintain engagement among youth with DS in the control group, they will be provided with three books to read independently or with their family during the waiting period. After the 8-week wait, control group participants will be invited to join the shared reading sessions. At that point, each young people with DS in the control group will be introduced to their student partner and may then participate fully in the weekly sessions. This approach ensures that while the control group receives books, they do not engage in dyadic shared reading until after the 8-week waitlist period. This design is methodologically critical, aligns with PPI group consensus that all participants eventually receive the intervention, and fulfills ethical requirements.

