### Outcome measures

Outcome measures will be collected at baseline (T0) and 8 weeks post-randomization (T1) for both the intervention and control groups. Following the initial 8-week RCT phase, all participants (including those from the waitlist control group) will receive the intervention; additional follow-ups will be conducted at 6 months (T2) and 12 months (T3) post-randomization in this single-arm extension phase. For the intervention group, outcomes for participants with DS will be collected at the end of the final session through researcher-administered interviews. For the control group, 8-week outcomes for participants with DS will be collected via researcher-conducted telephone interviews. University student participants in both groups will complete their outcome measures through an online survey, with reminder prompts sent after 1 and 2 days if not completed.

At T1, dyads in the intervention group will complete one additional measure (assessing the dyad's overall friendship) that will not be administered to the waitlist control group; all other outcome measurements are identical for both groups. The primary outcome of this study is the health-related quality of life of young people with DS at 8 weeks (T1), measured using the Pediatric Quality of Life Inventory (PedsQL)4.0. Secondary outcomes include the mental wellbeing of the student partners (assessed using the EPOCH scale) and the quality of the friendship within the dyad (assessed via the Friendship Quality Questionnaire, FQQ). Additionally, caregivers of participants with DS will complete a Global Perceived Effect (GPE) scale to evaluate their perception of change in the quality of life of the participant with DS.

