### Baseline characteristics

Baseline measurements will be recorded prior to randomization. Participant characteristics, including age, sex, height (cm), weight (kg), ethnicity, language, type of residence, and education level, will be collected. Caregiver information will also be recorded, including the caregiver's relationship to the participant and caregiver age. All outcome data collection points throughout the study timeline are presented in Table 1.

**Table 1 T1:** Data collection components and collection timeline.

**Construct**	**Outcome measure**	**Group**	**Baseline (T0)**	**8 weeks (T1)**	**6 months (T2)**	**12 months (T3)**
Socio-demographics		All participants	√	–	–	–
Health-related QoL	PedsQL 4.0	DS participants	√	√ (I+C)	√	√
		University students	√	√ (I+C)	√	√
Mental wellbeing	EPOCH	University students	√	√ (I+C)	√	√
Global perceived effect	GPE	DS caregivers	–	√ (I+C)	√	√
Friendship quality	FQQ	Intervention dyads only	–	√ (I)	√	√

DS, Young people with Down syndrome; I, Intervention group; C, Control group; PEDSQL 4.0, Pediatric Quality of Life Inventory version 4.0; EPOCH, Engagement, Perseverance, Optimism, Connectedness, and Happiness; GPE, The Global Perceived Effects scale; FQQ, Friendship Quality Questionnaire.

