### Statistical analysis

A target sample size of 12 dyads (12 per group) was selected to provide preliminary estimates of variability and feasibility, consistent with recommendations for pilot trials (26, 27), while remaining pragmatic given resource constraints in DS population studies. Statistical analysis will be performed by a researcher blinded to group allocation, and an independent statistician will verify the primary outcome analysis. The primary analysis will compare the shared book reading intervention group and the waitlist control group for the primary outcome at 8 weeks post-randomization. Secondary analysis will include analysis of secondary outcomes at 8 weeks post-randomization. Additionally, we will use an actor–partner interdependence model (APIM) to explore within-dyad relationships (examining how one member's baseline quality of life or mental wellbeing might influence both their own and their partner's outcomes). Dyad composition and potential differences in interpersonal dynamics will be accounted for within the APIM. For outcome comparisons, we will use mixed-effects linear models to account for repeated measures and dyad clustering, and results will be presented as mean differences between groups with 95% confidence intervals. Models will adjust for baseline scores in outcomes and covariates, including age, sex, and education level.

The primary analysis will be conducted using an intention-to-treat (ITT) approach. Secondary analyses will be performed after imputation of missing data. A sensitivity analysis will be conducted using multiple imputations for missing data (including all secondary outcomes and covariates in the imputation model). All analyses will be performed using R in RStudio (28).

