Feasibility of the RCT will be evaluated based on participant adherence to the intervention and completion rates of outcome measures at each time point. Acceptability of the intervention will be assessed through qualitative feedback from participants in the intervention arm. Caregiver presence and group size will be documented and analyzed as potential moderators of intervention effects. We will maintain continuous consultation with the PPI panel throughout the study to gain insights into intervention implementation. This ongoing feedback will help researchers understand factors that encourage or discourage participation, improving study processes for consideration in future studies. We will also involve the PPI panel in disseminating findings, incorporating their input when presenting results to local stakeholders.

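### The imputation model takes in FQQ, which is undefined for controls at 8 weeks, and session attendance by caregivers cannot be tested as a moderator of the 8-week intervention effect

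*Protocol article*

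**What the plan says.** **FQQ.** The Outcome measures section lists among the secondary outcomes "and the quality of the friendship within the dyad (assessed via the Friendship Quality Questionnaire, FQQ"). It describes the same instrument as an additional 8-week (T1) measure "that will not be administered to the waitlist control group". The FQQ row of Table 1 (Baseline characteristics) is labelled "Intervention dyads only". The Control group section gives the reason: "Dyads in the control group will not be introduced during this 8-week period".

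**Imputation.** The Statistical analysis section specifies multiple imputation as a sensitivity analysis, "including all secondary outcomes and covariates in the imputation model", with no exception for FQQ. It also says "Secondary analyses will be performed after imputation of missing data", so imputation is not confined to the sensitivity analysis. For outcome comparisons in general, "results will be presented as mean differences between groups with 95% confidence intervals".

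**Moderators.** The closing paragraph of that section, mainly on feasibility and acceptability, says: "Caregiver presence and group size will be documented and analyzed as potential moderators of intervention effects". Caregiver attendance is mentioned only in the section on the shared book reading intervention, as optional attendance at sessions. Group size is not defined. The Study design section allows pairings of one participant with DS to one or to two students, and the abstract places the forming of dyads before randomisation.

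**The concern.** Both problems come from using a variable that one arm does not have.

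A control participant's FQQ at T1 is not a value that exists and went unrecorded. There is no friendship to rate. A model that treats it as missing data must invent it, and in a chained imputation the invented values can then help predict missing PedsQL or EPOCH scores.

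A moderator of an intervention effect is a variable across whose levels the difference between arms changes. That requires the variable to be defined in both arms and not to be a consequence of allocation. Caregiver presence at sessions meets neither condition before T1.

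The pilot exists to inform a definitive trial. An association seen only among intervention dyads, reported as moderation, could be taken as evidence on caregiver involvement that the design cannot give.

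**Working it through.** The protocol gives no figure to reproduce here: the sample size rests on pilot-trial recommendations, without a power calculation. The question is whether the planned quantities can be estimated at all.

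**Inputs.** Allocation is 1:1 (Study design). The target of 12 dyads, followed by 12 per group (Statistical analysis), can be read as n = 6 or n = 12 dyads per arm, so both are used. Assumptions: outcome in SD units, one independent observation per dyad, and the binary moderator M split evenly.

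**1. FQQ in the imputation model.** Regress FQQ on an intercept, arm and one other predictor. FQQ is observed only in the intervention arm, where arm = 1 in every row, so the arm column equals the intercept column. The rank is 2 of 3 for n = 6 and n = 12. The arm coefficient is not identified, and no control row informs the prediction for controls. Share of dyads affected: n / 2n = 50%.

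**2. Caregiver presence at sessions.** The model needed is intercept, arm, M and arm × M. In controls M is constant; coded 0, it makes arm × M identical to M. The rank is 3 of 4 at either sample size. If M is instead coded missing in controls, their rows drop out and arm becomes constant, with the same result. More dyads would not help.

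What remains is a comparison of intervention dyads with and without caregiver presence, n/2 in each subgroup:

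- SE = √(2/n + 2/n) = √(4/n)
- n = 12: √(4/12) = 0.58 SD
- n = 6: √(4/6) = 0.82 SD

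**3. Group size, two readings.**

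- *Number attending a session.* This exists only in the intervention arm before T1, so step 2 applies.
- *1:1 or 1:2 pairing.* This is formed before randomisation and defined in both arms. The rank is 4 of 4, so the interaction is estimable. With four cells of n/2 dyads, SE = √(4 × 2/n) = √(8/n).

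| Dyads per arm | SE of interaction | Detectable with 80% power, two-sided 5%: (1.96 + 0.84) × SE |
|---|---|---|
| 12 | √(8/12) = 0.82 SD | about 2.3 SD |
| 6 | √(8/6) = 1.15 SD | about 3.2 SD |

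An uneven split between the two pairing types would widen these figures.

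**The case against.** The best defence has four parts.

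*The protocol already restricts FQQ to intervention dyads, so an analyst would treat control values as not applicable and could impute within arm.* Those are ordinary solutions, and it would be wrong to say that the imputation must fail. But the text fixes the content of the imputation model and makes no exception. This is a stated rule that does not work as written, not a detail left for later.

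*No arm-by-moderator term is specified, and the sentence sits among implementation measures.* This is fair as to intent. The sentence nevertheless names moderation of intervention effects, and at 8 weeks the only effect with a comparator is the difference between arms.

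*Controls are offered the sessions after 8 weeks, so session variables later exist for both original arms.* This is true, but the protocol calls that phase single-arm. It can show associations with change from baseline, not modification of a randomised contrast.

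*The stakes are small.* This largely stands. The protocol says that differences will be interpreted cautiously, and the moderator analysis is exploratory.

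Several stronger readings are tempting, and the document does not support them:

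- **Group size exists only in the intervention arm.** The term is undefined. The separate mention of dyad composition in the actor–partner model makes session size the likelier meaning but does not settle it.
- **Caregivers attend when a participant struggles.** The protocol says only that they are welcome. Confounding is possible, but the non-estimability does not depend on it.
- **A between-arm comparison of FQQ is planned.** This follows only from the general wording on outcome comparisons and is never stated for FQQ.
- **The imputation model is over-fitted.** About ten variables (PedsQL and EPOCH at two times each, GPE, FQQ, age, sex, education, arm) against 12 or 24 dyads is a reason for care. No effect on any result has been shown.

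**Conclusion.** The point holds in a limited form. Taken literally, the imputation model contains a variable that is undefined for half the dyads, with its control values unidentified. The interaction of arm with caregiver presence at sessions cannot be estimated at 8 weeks, whatever the sample size. For group size the conclusion depends on its meaning: not estimable as session size; estimable but of little practical use as dyad size, with a standard error of 0.82 to 1.15 SD.

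The non-estimability rests on caregiver presence meaning attendance at sessions, the only sense the protocol describes, and on control dyads having no sessions before T1, which it states. The standard errors rest on the even-split and independence assumptions given above.

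The consequences are confined to the imputation-based analyses (the secondary analyses and the sensitivity analysis) and the exploratory moderator analysis. A reader might infer that the primary result is compromised. The document does not support that: the primary analysis is an intention-to-treat comparison of PedsQL, imputation is assigned to the secondary and sensitivity analyses, and no effect on the primary comparison has been shown. The point should be corrected, but it does not threaten the trial's main comparison.

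**What to change.** 1. **Imputation.** State that FQQ is excluded from the imputation model and is reported descriptively in the intervention arm at T1. Keep arm, the available baseline scores, age, sex, education and dyad clustering in the imputation. Age, sex and education are covariates of the analysis models, so an imputation model without them would be poorer than the analysis it serves. GPE has no baseline measurement in Table 1, so its imputation cannot condition on its own baseline value.
2. **Use of imputation.** Say how the imputation that precedes the secondary analyses differs from the multiple-imputation sensitivity analysis, or that they are the same.
3. **Session-level variables.** Report caregiver presence and session size as implementation measures, or as non-randomised associations within the intervention arm.
4. **Moderators.** Define group size. Reserve the word moderator for variables fixed before randomisation, such as dyad size if that is what is meant, and report any such interaction as an estimate with its confidence interval.

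The cost is a few sentences of analysis wording, with no change to data collection. The downside is that no moderator claim can be made for caregiver presence, which the data could not have supported.

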### Data confidentiality

All information related to the trial will be securely stored at the research center of the Faculty of Health Sciences, University of Macau. Data will be anonymized using coded identification numbers. These codes will be stored separately under password protection to prevent identification of individual participants. Access to the data will be limited to a small number of personnel responsible for quality control, auditing, and analysis. The final trial dataset will only be accessible to the study statistician.

## Discussion

### Anticipated contributions

Our study adopted a PPI approach, engaging two parents, one young people with DS, two university students in an iterative consultation process, subsequently joined by one MDSA representative and three additional undergraduates. Initial consultations revealed stakeholder recommendations to utilize social media platforms (e.g., DS-focused Facebook groups) and MDSA newsletters for recruitment, with 85% of caregivers preferring Sunday afternoon sessions to avoid scheduling conflicts with educational/therapeutic commitments. Young participants emphasized incorporating engaging activities (e.g., games) to maintain involvement. Subsequent consultations refined the intervention protocol through: (i) inclusion of visually enriched books (e.g., Unusual Friends) and graphic novels as suggested by PPI members; (ii) co-development of a parent-proposed “growth record” logbook with visual prompts (e.g., emoticons); and (iii) implementation of a 1-h DS-specific communication training for student volunteers covering simplified language and visual supports. Protocol modifications included introducing 10-min icebreaker activities (e.g., adapted musical chairs), structured dyadic reflection periods, replacement of lengthy quality-of-life measures with PedsQL 4.0 (short form), and addition of the FQQ per parental requests. A PPI advisory group (two parents, two DS youth, three students) meets quarterly to monitor adherence (e.g., attendance records) and troubleshoot implementation challenges (e.g., introducing audiobooks for reading difficulties), while contributing to knowledge dissemination through plain-language summaries. While acknowledging potential selection bias (e.g., overrepresentation of highly educated participants), diversity was enhanced through MDSA's outreach initiatives, demonstrating PPI's comprehensive influence across intervention design, implementation, and evaluation.

The goal of this study is to assess the potential feasibility and possible effects of shared book reading as a simple, low-cost intervention to improve the mental wellbeing and quality of life for young people with and without DS. We chose shared book reading because it is an easy-to-implement, broadly applicable activity that enhances participants' overall wellbeing by promoting emotional connections, enhancing social interaction, and providing psychological support. As a pilot study, this research will primarily inform the feasibility of conducting a larger future trial—including acceptability for recruitment, adherence to weekly sessions, and completeness of data collection—and provide initial indications of effect sizes for outcomes of interest. Shared book reading is a non-invasive, low-intensity intervention that requires no complex equipment or professional technical support and can be easily implemented in various settings.

This simplicity makes the shared book reading intervention particularly appealing, with potential for scalability, especially in resource-limited settings for long-term sustained implementation. We anticipate high participant acceptability based on initial PPI feedback indicating positive reception of the concept. Given its non-invasive nature and early positive reception, we believe the intervention will be both feasible and acceptable in practice. While we do not anticipate major implementation challenges, this will be formally evaluated in the pilot study.

### Strengths of the study design

A key strength of our study design is that the shared book reading intervention was developed with in-depth guidance from patients and PPI representatives. Through multiple rounds of discussion, we incorporated perspectives from different stakeholders. For example, caregivers of individuals with DS shared their experiences and expectations for reading activities, public representatives provided feedback on general community acceptance of such programs, and researchers ensured the intervention format was evidence-based and effective. The final intervention protocol represents a truly collaborative product, refined repeatedly through follow-up PPI meetings to maximize the positive benefits of reading and create a comfortable physical and mental environment for participants.

### Addressing gaps in literature

Recent research suggests that interventions aiming to develop language skills in people with DS can indeed improve communication (29). Such interventions can take many forms, including incorporating books and magazines into regular activities and providing adequate guided practice (30). Previous meta-analyses have shown that language interventions, like shared book reading, can improve spoken language ability in children with neurodevelopmental disorders (31). Interventions included in these meta-analyses used various techniques, including shared reading, general language stimulation, direct language instruction, play-based language interventions, multimedia-assisted interventions, social interaction-based interventions, and family-involved interventions. Meta-regression indicated that longer sessions over extended periods were more beneficial than shorter, short-term interventions. This finding informed our decision to implement relatively longer sessions over an 8-week period in our trial, with the expectation that a sustained intervention could lead to larger effect sizes. Although our pilot is not fully powered to detect statistically significant differences, it will provide effect size estimates to inform the sample size of a future definitive RCT.

### Implications for practice and policy

Shared book reading among young people with DS has received less empirical attention than among typically developing adolescents (32). Given the prevalence of language learning difficulties among young people with DS, adjustments in how shared book reading is conducted may be necessary to maximize its effect. In our study, we chose books that combine pictures with text, as evidence suggests these format benefits individuals with DS by compensating for poorer verbal short-term memory through stronger visuospatial memory (33). Lack of motivation and difficulty maintaining focus are commonly reported barriers to reading activities with children with DS (34). Our inclusion of interactive games and the growth logbook in the intervention is partly intended to address these issues by making sessions enjoyable and rewarding. Our pilot will also explore areas that remain unclear in the literature—for example: potential long-term benefits of shared reading; whether effects differ between participants with DS and their student partners; how cultural context might influence outcomes; and the overall sustainability and acceptability of such interventions (35). In summary, this study will yield valuable information for future intervention research. Findings on feasibility and acceptability will guide the design and implementation of larger studies. Ultimately, we aim to establish shared book reading as a viable, evidence-based strategy to improve mental wellbeing and quality of life in young people both with and without DS.

### Potential strengths and limitations

Shared book reading represents a simple, low-cost intervention, and this study constitutes the first attempt to partner young people with DS and university students in a collaborative reading program. This approach is significant because a single intervention targeting both populations may generate sustainable positive effects for both groups. Additionally, this will be the first study conducted in Macau focusing on this specific population, and as such, recruitment rates and expected adherence remain uncertain. The intervention, jointly designed through PPI, demonstrates significant advantages. These findings hold important policy implications, particularly regarding the scalability of this low-cost, community-based model for other neurodevelopmental disorders in resource-limited settings. By demonstrating benefits for both adolescents with disabilities and student partners, it has potential to inform inclusive education policies and provide opportunities for health system integration. Future implementation should focus on promoting the standardized of personnel training and ensuring equitable access to appropriate reading materials and technologies.

However, several limitations should be acknowledged. First, the use of a waitlist control design, rather than an active concurrent control, may introduce potential bias, as control group participants will eventually receive the intervention. This design also raises the possibility of contamination, as control group participants may have access to books and opportunities to engage in shared reading with others outside the study. Second, blinding of participants to their group allocation (intervention or control) is not feasible, which may lead to differing expectations of improvement and influence outcomes during data collection. Finally, challenges related to recruitment and participant retention are anticipated, which could impact the study's overall feasibility and generalizability. As a pilot study, the sample size is limited, and the study may be underpowered to detect modest intervention effects. Consequently, any outcome differences will be interpreted cautiously and primarily used to inform the design of a larger trial. Despite these limitations, this pilot study represents an important first step in evaluating an innovative intervention. The insights gained will be invaluable for planning a definitive trial and could open new avenues for mental wellbeing promotion in young people with developmental disabilities (36).

